### Participant timeline {13}

Table 3 presents the schedule for the enrollment, interventions, assessments, and visit of the participants.

**Table 3 Tab3:** Schedule of the major study events

Project	Gastroscopy diagnosis and treatment period(Visit 1)					
	Arrive the examination room	sedative induction	Procedure start	Procedure over	participants wakes up	Leave the examination room
**Baseline data**						
Informed consent	**×**					
Medical history	**×**					
Inclusion / exclusion criteria	**×**					
Demographic data	**×**					
Vital signs	**×**	**×**	**×**	**×**	**×**	**×**
Physical examination	**×**					
**Research outcome measures**						
Hypoxia		**×**	**×**	**×**		
Sub-clinical hypoxia		**×**	**×**	**×**		
Severe hypoxia		**×**	**×**	**×**		
Adverse event		**×**	**×**	**×**		
**Research drug**						
Study randomization	**×**					
Calculate drug dosage						**×**
**Others**						
Gastroscope procedure time				**×**		
Combined medication	**×**	**×**	**×**	**×**	**×**	**×**

When the participants will enter the gastrointestinal endoscopic operating room, they will be screened for eligibility by the investigator. If they meet the inclusion criteria but not the exclusion criteria, the investigator will provide them with the fully informed consent form. After signing the informed consent form, the patients will be allocated to either the capnographic monitoring group or the control group via the central randomization system.

In the capnographic monitoring group, the criteria for apnea is the absence of exhaled CO_2_; altered ventilation is defined as end-tidal CO_2_ reduced by more than half of the baseline, as shown by the capnogram; and the definition of hypoxia is 75%<SpO_2_ < 90%, <60s. In the control group, hypoxia is defined as SpO_2_ <90%.

In both the groups, any sign of apnea, altered ventilation, or hypoxia that prompts an intervention will comprise (i) increasing oxygen supplementation, (ii) a chin lift or jaw thrust maneuver, (iii) insertion of the oropharyngeal or nasopharyngeal airway with a chin lift or jaw thrust maneuver, (iv) artificial mask ventilation, and (v) tracheal intubation.

The duration of surgery is defined as the time from the beginning to the end of the gastrointestinal endoscopy, excluding the time of resuscitation.

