### Objectives {7}

Our aim is to investigate whether an additional capnographic monitoring-based intervention can reduce hypoxia incidence in older patients undergoing gastrointestinal endoscopy under sedation. Our primary objective is to measure the incidence of hypoxia (75% ≤ SpO_2_ < 90% for < 60 s). Our secondary objective is to measure the incidences of subclinical respiratory depression (90% ≤ SpO_2_ < 95%), severe hypoxia (SpO_2_ < 75% or 75% ≤ SpO_2_ < 90% for ≥60 s), and other adverse events (AEs) recorded via tools proposed by the World Society of Intravenous Anesthesia International Sedation Task Force. We predict that additional capnographic monitoring of ventilatory activity will reduce hypoxia incidence during propofol sedation for gastrointestinal endoscopy in older patients. Our aim is to provide credible evidence regarding reduced hypoxia incidence in older patients.

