**Step 2: Please DESCRIBE the adverse event(s). Check all that apply.**				
**Minimal risk descriptors**	**Minor risk descriptors**		**Sentinel risk descriptors**	
□ Vomiting/retching	□ Oxygen desaturation (75–90%) for < 60s		□ Oxygen desaturation, severe (<75% at any time) or prolonged (<90% for >60s)	Other, specify below
□ Sub-clinical respiratory depression^a^	□ Apnoea not prolonged		□ Apnoea, prolonged (>60s)	
□ Muscle rigidity, Myoclonus	□ Airway obstruction		□ Cardiovascular collapse/shock^g^	
□ Hypersalivation	□ Failed sedation^e^		□ Cardiac arrest/absent pulse	
□ Paradoxical response^b^	□ Allergic reaction without anaphylaxis			
□ Recovery agitation^c^	□ Bradycardiat^f^			
□ Prolonged recovery^d^	□ Tachycardia^f^			
	□ Hypotension^f^			
	□ Hypertension^f^			
	□ Seizure			

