### Outcomes {12}

#### Primary outcome measures

The primary outcome of this study is the incidence of hypoxia (75% ≤ SpO_2_ < 90% for <60 s) in the two groups from the beginning to the end of the operation.

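### The participant timeline defines hypoxia differently in the two arms, contradicting the single primary-outcome definition; used for coding, it would bias the comparison toward capnography

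*Protocol article*

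**What the plan says.** - **Outcomes {12}, primary outcome:** one definition for both arms: "The primary outcome of this study is the incidence of hypoxia (75% ≤ SpO_2_ < 90% for <60 s) in the two groups". Objectives {7} gives the same limits without reference to arm: "Our primary objective is to measure the incidence of hypoxia (75% ≤ SpO_2_ < 90% for < 60 s").
- **Outcomes {12}, secondary outcomes:** SpO2 below 75%, or 75% to below 90% lasting 60 s or more, is severe hypoxia. It is a separate outcome, again for both groups.
- **Table 2, Step 2:** the adverse-event form is common to both arms. It has a minor-risk box, "Oxygen desaturation (75–90%) for < 60s", and a separate sentinel box for severe or prolonged desaturation.
- **Participant timeline {13}, text after Table 3:** for the capnography group, and then for control, "the definition of hypoxia is 75%<SpO_2_ < 90%, <60s. In the control group, hypoxia is defined as SpO_2_ <90"%. The paragraph after that begins "In both the groups, any sign of apnea, altered ventilation, or hypoxia that prompts an intervention will comprise" and lists oxygen and airway measures.
- **Who will be blinded {17a}:** participants only.

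**The concern.** Read literally, the timeline classifies the same event differently by arm. A patient who falls to 70%, or who stays at 85% for 90 s, has hypoxia if allocated to control. The same patient does not meet the hypoxia definition if allocated to capnography. The term is also the name of the primary endpoint.

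If this wording reached the case report form or the coding instructions, the control count would include severe and prolonged cases that the capnography count leaves out. The error runs in one direction, toward the hypothesis. Blinding of outcome recorders cannot protect against it, because only participants are blinded. Trial status gives a recruitment start in September 2021 and an end in December 2023, so records may already exist under either wording.

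**Working it through.** **1. The definitions side by side**

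| Place | Arm | Lower limit | Upper limit | Duration |
|---|---|---|---|---|
| Objectives {7} | not arm-specific | 75% included | below 90% | under 60 s |
| Outcomes {12}, primary | both | 75% included | below 90% | under 60 s |
| Table 2, minor-risk box | common form | 75%, inclusion not stated | 90%, inclusion not stated | under 60 s |
| Timeline {13} | capnography | 75% excluded | below 90% | under 60 s |
| Timeline {13} | control | none | below 90% | none |

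The control row agrees with no other row. There are smaller mismatches too. A reading of exactly 75% is hypoxia under Outcomes but not under the timeline's capnography wording. An episode of exactly 60 s is severe under the secondary outcome, but Table 2 calls desaturation prolonged only beyond 60 s, so it fits neither Table 2 box unless SpO2 falls below 75%.

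**2. The plan's own figure**

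Inputs from Sample size {14}: 8% against 4%, 1:1 allocation, 90% power, two-sided 5%, 10% dropout.

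- Uncorrected: n = [1.96·√(2·0.06·0.94) + 1.2816·√(0.08·0.92 + 0.04·0.96)]² / 0.04² = 738.7, so 739 per arm.
- Continuity-corrected: n′ = (n/4)·[1 + √(1 + 4/(n·0.04))]² = 788 per arm, 1576 in total.
- Dropout: 1576/0.9, rounded up per arm, gives 1752, consistent with the stated figure of about 1800.

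The sample size is not in dispute. Evaluable patients: 1800 × 0.9 / 2 = 810 per arm.

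**3. What arm-specific coding would do**

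Assume no true effect, with 8% of each arm having any SpO2 below 90%. Let s be the share of those patients whose events are *only* severe or prolonged. The documents do not give s, so a range is shown. A patient who also had a brief episode within the limits is taken to count in either arm, so only the exclusive cases are lost.

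- Control rate: p_c = 0.08
- Capnography rate: p_t = 0.08·(1 − s)

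Normal approximation at s = 0.20:
- p_t = 0.064, difference = 0.016, mean rate = 0.072
- SE under the null = √(2·0.072·0.928/810) = 0.01284; the unpooled SE is also 0.01284
- P(significant in favour of capnography) = Φ[(0.016 − 1.96·0.01284)/0.01284] = Φ(−0.715) = 23.7%

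Exact binomial enumeration, 810 per arm, two-sided 5%:

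| s (assumed) | Capnography rate | Apparent risk ratio | False positive, Pearson χ² | False positive, continuity-corrected χ² |
|---|---|---|---|---|
| 0 | 8.0% | 1.00 | 5.0% | 4.0% |
| 5% | 7.6% | 0.95 | 6.0% | 4.9% |
| 10% | 7.2% | 0.90 | 9.2% | 7.8% |
| 20% | 6.4% | 0.80 | 23.7% | 21.0% |
| 25% | 6.0% | 0.75 | 35.0% | 31.7% |

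Both tests are allowed by the Statistical analysis plan subsection of {20a}. From s = 10% upward nearly all of the rejections favour capnography. The row s = 0 is also what results if the Outcomes definition is used in both arms.

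**The case against.** The strongest reply is that the timeline sentences are intervention triggers, loosely drafted, and not outcome definitions. They stand beside the criteria for apnea and altered ventilation, neither of which is among the listed hypoxia outcomes, and they lead straight into the list of measures taken when such a sign appears. Wherever the outcome is defined as an outcome, it is uniform: Objectives, Outcomes, the separate rows in Table 3, and the common form in Table 2. The statistical section also compares hypoxia, severe hypoxia and total hypoxia as separate variables.

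Much of this stands. A reader might infer that the trial has an arm-specific endpoint and that its 5% error rate is already lost. The documents do not support that: the Outcomes section says otherwise, and no section says that staff code from the timeline text.

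The reply does not remove the contradiction. The sentences are phrased as definitions of hypoxia. A limit of under 60 s can be confirmed only once an episode is over, which suits classification better than a trigger. They follow a table that lists hypoxia as a research outcome. Even as triggers, they would give the two arms different SpO2 criteria under the name of the primary endpoint, and the text never states their role.

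**Conclusion.** The point holds as an internal contradiction on the primary outcome. The timeline wording cannot be squared with the Objectives and Outcomes sections, nor with severe hypoxia as a separate outcome in both groups, and its role is left open.

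The bias is conditional on the timeline text being used to code the outcome. Under that condition it favours capnography, with a false-positive rate of about 6%, 9%, 24% or 35% for assumed shares of 5%, 10%, 20% or 25%. These figures rest on 8% with any desaturation in both arms, 810 evaluable per arm, the Pearson chi-square test, and a share that the documents do not report. The relevant share is patients with exclusively severe or prolonged events. It cannot exceed the share with any such event and may be much smaller. If the Outcomes definition governs in both arms, this bias is absent.

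**What to change.** 1. State that the primary-outcome definition in Outcomes {12} applies identically to both arms for all outcome recording. Make the boundaries at 75%, 90% and 60 s agree across Objectives, Table 2, the primary and secondary outcomes, and the timeline.
2. In the timeline, remove the arm-specific outcome wording, or label it explicitly as intervention-trigger text. If it is trigger text, reconcile it between the arms. Which trigger is right is a clinical matter and is not judged here.
3. Check records already completed against the single definition, as far as the SpO2 data held allow. Table 3 schedules vital signs at six points and the protocol does not promise stored continuous readings, so full re-coding may not be possible. Where it is not, report which wording was in use.

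The cost is an amendment to the protocol and, if affected, the case report form. It needs the ethics committee's consent under the protocol's own amendment rule, plus the effort of the record check. No patients or procedures are added, and the sample size is unchanged.

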### Sample size {14}

Our previous study revealed that hypoxia incidence in patients during gastrointestinal endoscopy with propofol sedation was ~8 % [11]. The anticipated effect size of additional capnographic monitoring was 50%, implying that the hypoxia incidence power analysis assumes a reduction from 8% to 4%. The results of a conventional analysis were compared between the capnography-open and capnography-blinded groups to detect differences in proportions (hypoxia). We use PASS 11.0, randomization 1:1, power of 1 − β = 0.90, and a two-sided α level of 5%. We assume a 10% dropout rate. Thus, the results revealed that ~1800 patients would be required.

### Recruitment {15}

The schedule of the major study events for each study visit is presented in Table 3. This study included older patients who are scheduled to undergo gastrointestinal endoscopy with propofol sedation. The patients (65 ≤ age <80 years) who met the inclusion criteria were preliminarily screened by the investigators and recruited by distributing recruitment materials to patients and their families. Additionally, we put up recruitment posters in the endoscopy centers explaining the advantages of our trial. The nasal catheters that will be used in our trial are free, and the trial is beneficial for participants. We estimate that the trial will easily recruit enough participants according to the number of patients admitted to the endoscopy centers per day.

The entire process of recruiting participants and obtaining their consent by the members of the research team will be consistent with GCP.

## Assignment of interventions: allocation

### Sequence generation {16a}

In this trial, we used stratified blocked randomization to design the central randomization system. Risk factors for hypoxia during sedated gastrointestinal endoscopy include patient factors, sedation factors, and endoscopic operation factors. Patient factors mainly include preexisting cardiopulmonary disease, obesity, and advanced age. The incidence of hypoxia during sedated gastrointestinal endoscopy varies among patients with different underlying conditions. However, the subjects in our trial were all ASA I–II patients and did not include patients with ASA III-IV, which means that the trial did not involve patients with previous severe cardiopulmonary disease. Additionally, the number of obese patients in the older population in China is extremely low, and stratification by obesity would provide little benefit. Our study only included ASA I–II older patients aged 65 to 80 years, who we can assume have similar physical conditions, and the incidence of hypoxia during sedated gastrointestinal endoscopy is approximately the same. Therefore, we did not stratify them by age, and only central stratification was used in our trial. Complete baseline data will be collected from participants, including name, gender, date of birth, etc. After assessing patient eligibility for inclusion, his/her informed consent will be obtained. We will randomly assign the participants in a ratio of 1:1 to the standard or additional capnographic monitoring group according to the allocation sequence of the central randomization system. The length of a random sequence is not fixed, and 4, 6, and 8 are random.

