### Eligibility criteria {10}

This clinical trial has three centers that recruited patients. A summary of the inclusion and exclusion criteria is presented in Table 1.

**Table 1 Tab1:** Inclusion/exclusion criteria

Inclusion criteria	Exclusion criteria
1) Aged ≥65 and <80 years	1) Coagulation disorders or a tendency of nose bleeding
2) Scheduled to undergo gastrointestinal endoscopy procedure with sedation	2) An episode/exacerbation of congestive heart failure that requires a change in medication, diet, or hospitalization from any cause in the past 6 months
3) Signed the informed consent form	3) Severe aortic stenosis or mitral stenosis
4) American Society of Anesthesiologists (ASA) classification I-II	4) Cardiac surgery involving thoracotomy (e.g., coronary artery bypass graft, valve replacement surgery) in the past 6 months
	5) Acute myocardial infarction in the past 6 months
	6) Acute arrhythmia (including any tachycardia or bradycardia) with fluid of hemodynamics instability
	7) Diagnosed with chronic obstructive pulmonary disease or current other acute or chronic lung disease requiring supplemental chronic or intermittent oxygen therapy
	8) Preexisting bradycardia (heart rate <50/min), or hypoxia (SaO_2_ < 90%)
	9) Need supplemental oxygen because of preexisting diseases
	10) Emergency procedure or surgery
	11) Multiple trauma
	12) Upper respiratory tract infection
	13) Allergy to propofol or tape and adhesives

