#### Statistical analysis plan

All statistical analyses in this trial will be programmed and calculated using Statistical Package for the Social Sciences version 23.0 (IBM Inc., Armonk, NY, USA). The normally distributed baseline continuous data will be represented by mean (standard deviation [SD]) and compared by using an unpaired *t*-test. The non-normally distributed continuous data will be presented as median (interquartile range [IQR]) and compared by using Mann–Whitney *U* test. We will use χ^2^ test, continuity correction *χ*^2^ test, or Fisher’s exact test to analyze the categorical variables. We intend to compare the incidences of hypoxia, subclinical hypoxia, severe hypoxia, and total hypoxia of the participants during gastrointestinal endoscopy under sedation via *χ*^2^ test, continuity correction *χ*^2^ test, or Fisher’s exact test.

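### The primary hypoxia comparison is unadjusted although age, centre and very probably arrival SpO2 are available; prespecified adjustment would be a small, nearly free gain in precision

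*Protocol article*

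**What the plan says.** **Primary comparison.** In the protocol article, Statistical analysis plan (under item 20a): "We intend to compare the incidences of hypoxia, subclinical hypoxia, severe hypoxia, and total hypoxia of the participants during gastrointestinal endoscopy under sedation". The tests listed are chi-square, continuity-corrected chi-square and Fisher's exact. No covariate and no centre term is named.

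**Adjusted analysis.** The section on additional analyses (item 20b) plans univariable and multivariable logistic regression on baseline characteristics and intervention, with odds ratios and 95% CIs. Its outcome is total hypoxia. The primary outcome (item 12) is the narrower band of SpO2 from 75% to below 90% lasting under 60 s.

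**Risk factors and strata.** Sequence generation (item 16a) says: "Patient factors mainly include preexisting cardiopulmonary disease, obesity, and advanced age". It then describes the ASA I–II patients aged 65 to 80 as people "who we can assume have similar physical conditions, and the incidence of hypoxia during sedated gastrointestinal endoscopy is approximately the same". From this it concludes that randomisation need not be stratified by age, and uses centre as the only stratum.

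**What is collected.** Item 16a lists date of birth among the baseline data, and the consent section (item 26a) places baseline collection before allocation. Table 3 schedules "Demographic data" and vital signs on arrival. The intervention description (item 11a) makes SpO2 part of standard monitoring in both arms, and Table 1 excludes patients with a saturation below 90%. No passage says outright that an arrival SpO2 value is recorded on the case report form.

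**The concern.** Where baseline variables predict a binary outcome, an analysis that conditions on them estimates the risk difference at least slightly more precisely than a plain 2x2 table. It also accounts for a chance imbalance between arms in those variables. Here age is in hand, resting saturation lies on the same scale as the event threshold, and centre was used to stratify. The article already accepts adjusted logistic regression, but for another outcome and without naming covariates. If covariates for the primary outcome were chosen only after the data were seen, the adjusted result would carry less weight than a prespecified one.

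The equal-risk sentence is a separate, smaller matter. It is an assumption without cited data, it follows directly on a list of risk factors that includes age, and it could be read as evidence that age is not worth modelling. At stake are some precision and a more defensible primary estimate, not the validity of the trial.

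**Working it through.** **Inputs from the article (item 14).** Control risk 8%, intervention risk 4%, two-sided alpha 5%, "power of 1 − β = 0.90", 1:1 allocation, 10% dropout, about 1,800 patients.

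**Step 1: the stated sample size.** With p̄ = 0.06 and δ = 0.04:

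n = [1.960·√(2·0.06·0.94) + 1.282·√(0.08·0.92 + 0.04·0.96)]² / 0.04² = 739 per arm, or 1,478 in total. Dividing by 0.90 gives 1,643.

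With the continuity correction, n' = (n/4)·[1 + √(1 + 4/(nδ))]² = 788 per arm, or 1,576 in total. Dividing by 0.90 gives 1,752, which is 2.7% below 1,800. The plan's figure is therefore reproduced by the continuity-corrected formula.

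**Step 2: precision of the unadjusted comparison.** Evaluable patients: 1,800 × 0.90 = 1,620, or 810 per arm. Expected events: 810 × 0.08 + 810 × 0.04 = 97.2.

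SE = √[(0.0736 + 0.0384)/810] = 0.01176. The 95% half-width is 1.96 × 0.01176 = 2.31 points. Power = Φ(0.04/0.01176 − 1.96) = 92.5%.

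**Step 3: precision after adjustment.** Let p0 and p1 be a patient's risks under control and intervention given the covariates, with means m0 = 0.08 and m1 = 0.04. The large-sample variances, multiplied by the total N, are:

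- unadjusted: 2·m0(1 − m0) + 2·m1(1 − m1) = 0.224
- standardised logistic model: 2·E[p0(1 − p0)] + 2·E[p1(1 − p1)] + Var(p1 − p0)

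The article gives no predictor strengths and no SpO2 distribution. Assumptions: age uniform on 65–80; resting SpO2 with mean 97 and SD 1.5, kept within 90–100; odds ratios as shown. Centre is not in the calculation. Equivalent extra patients = 1,620/ratio − 1,620.

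| Age OR per 5 years | SpO2 OR per SD lower | Variance ratio | Reduction | Extra patients | Half-width (points) | Power |
|---|---|---|---|---|---|---|
| none | none | 1.0000 | 0% | 0 | 2.31 | 92.5% |
| 1.2 | 1.0 | 0.9986 | 0.1% | 2 | 2.30 | 92.6% |
| 1.2 | 1.3 | 0.9947 | 0.5% | 8 | 2.30 | 92.7% |
| 1.5 | 1.5 | 0.9833 | 1.7% | 27 | 2.29 | 92.9% |
| 2.0 | 2.0 | 0.9490 | 5.1% | 87 | 2.25 | 93.7% |
| 1.5 | 2.5 | 0.9386 | 6.1% | 106 | 2.23 | 94.0% |

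**Step 4: cross-check by simulation.** With 810 per arm, 3,000 runs per setting and the same kind of assumptions, a pooled z-test was compared with a logistic Wald test adjusted for age and SpO2. At 8% v 4%, power (unadjusted/adjusted) was 93.2/93.0 with weak predictors (AUC 0.60), 92.1/92.4 at AUC 0.68 and 92.7/94.3 at AUC 0.74. At 8% v 4.8% the pairs were 74.1/74.6, 75.3/77.2 and 76.8/78.6. The Monte Carlo standard error is about 0.5 to 0.8 points per figure, so this agrees with Step 3.

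**Step 5: what the equal-risk sentence implies.** With the control average held at 8%, an assumed age odds ratio of 1.2 per 5 years gives a control risk of about 6% at 65 and 10% at 80. An odds ratio of 1.5 gives about 4% and 13%. Risk is close to equal only if age has almost no effect in this range, and the article offers no data on that.

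**The case against.** The case for leaving the plan alone is substantial. Under randomisation the unadjusted test is valid, its error rate and confidence interval already allow for chance imbalance, and it matches the comparison of proportions behind the sample size. Power already exceeds the 90% target. Predictor strengths have to be assumed, and the largest gain needs an odds ratio of 2.5 per SD of SpO2. The primary outcome is also a band: low resting saturation may move some patients into the separate severe-hypoxia outcome, so it may predict the primary outcome less well than a simple threshold event. All of this stands. It limits the size of the point but does not remove it.

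Some stronger readings are tempting, and the article does not support them:

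- A reader might infer that the test is unadjusted because equal risk was assumed. The sentence sits in Sequence generation, and its stated conclusion concerns only stratification by age.
- A reader might infer that the article contradicts itself on age. Advanced age may mean older against younger adults, which is how the Introduction and Discussion use the contrast. The sentence is unsupported, not strictly contradictory.
- A reader might infer that no adjusted analysis is planned. One is, under item 20b, for total hypoxia.
- A reader might take a recorded arrival SpO2 as stated. It is a strong inference from the vital-signs row, the standard monitoring and the eligibility floor.

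A separate analysis plan, not available here, may already adjust the primary outcome. The article nevertheless names its test, so the point addresses a stated choice.

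**Conclusion.** The point holds as a minor improvement. The primary outcome is compared only with an unadjusted 2x2 test, and the planned adjusted model addresses a different outcome. With both covariates predictive, adjustment would reduce the variance of the risk difference by roughly 0.5% to 6%, and by less if only age matters, weakly. The gain in power at 8% v 4% is about 0 to 1.5 points. These figures rest on the assumed odds ratios and SpO2 distribution, on 1,620 evaluable patients and on a correctly specified model; any contribution from centre is not counted. No bias, invalid test or shortfall in power is shown, and the sample size need not change.

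The equal-risk sentence is an unsupported assumption. Its consequence in the article is limited to the choice of strata.

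**What to change.** Before any comparison of outcomes by arm:

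1. Confirm that arrival SpO2 is on the case report form, and define which reading counts (taken before sedation, and preferably before allocation is known).
2. Prespecify, for the primary outcome in the full analysis set, a logistic model with arm, centre, age (continuous) and arrival SpO2 (continuous). With three centres this is 1 + 2 + 1 + 1 = 5 terms for about 97 expected events, or about 19 per term.
3. Report the standardised risk difference and risk ratio with 95% CI, which keeps the result on the 8% v 4% planning scale.
4. Keep the chi-square test as a supportive analysis.
5. In Sequence generation, support the equal-risk sentence with data or delete it.

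If arrival SpO2 proves not to be recorded, the model can go ahead with arm, centre and age.

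**Cost.** No extra patients, and no new measurements if arrival SpO2 is already recorded. The change needs a protocol amendment with ethics committee consent (item 25). Because only participants are blinded and recruitment began in September 2021, the amendment should be dated and should state that no outcome data by arm had been examined.
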